| **(D) Follow-up period** | From 11 weeks’ gestation until 28 days post-birth. | From 11 weeks’ gestation until 28 days post-birth. |
| **(E) Outcomes** | **Primary Maternal**  Severe hypertension (systolic blood pressure ≥160mmHg).  **Primary Neonatal**  Composite of stillbirth, neonatal death (until 28 days post-birth), and NICU admission requiring separation of infant and mother (until 28 days post-birth).  **Secondary Maternal**  *Note: Variables denoted with a * are reported with treatment effect and 95% CI, all others are exploratory only and described with summary statistics*.   - Mean antenatal systolic blood pressure* - New diagnosis of preeclampsia* - Severe maternal morbidity (fullPIERS consensus definition)* - Discontinuation of allocated antihypertensive* - Undesirable effects of allocated antihypertensive* - Maternal death* - Indicated birth (induction of PROM)* - Mean antenatal diastolic blood pressure - Proportion of days with antenatal systolic blood pressure ≥140mmHg - Proportion of days with antenatal diastolic blood pressure ≥90mmHg - Diagnosis of eclampsia - Diagnosis of HELLP syndrome - Placental abruption - Components of severe maternal morbidity - Maternal stroke - Prescription of additional antihypertensive drugs - Prescription of alternative antihypertensive drugs - Time from randomization to first discontinuation of allocated antihypertensive - Total number of antenatal hospital inpatient days - Treatment satisfaction - Beliefs about allocated antihypertensive drug - Adherence to allocated antihypertensive drug - Mode of onset of birth   **Secondary Neonatal**  *Note: Variables denoted with a * are reported with treatment effect and 95% CI, all others are exploratory only and described with summary statistics*.   - Major congenital anomaly (as defined by EURO-CAT)* - Birthweight centile* - Need for treatment for neonatal hypoglycemia* - Neonatal unit admission (separation of baby from mother)* - Mode of birth* - Gestational age at birth* - Fetal loss <24^+0^ weeks’ gestation - Fetal loss ≥24^+0^ weeks’ gestation (stillbirth) - Known early neonatal death (up to 7 days post-birth) - Known late neonatal death (7-28 days post-birth) - Principal recorded indication for neonatal unit admission - Length of stay in neonatal unit (and level of care) - Indication for mode of birth - Preterm birth (<37 completed weeks) - Preterm birth (<32 completed weeks) - Birthweight - Birthweight SGA (<10^th^ centile) - Umbilical arterial pH<7 at birth - Apgar score 5min post-delivery - Need for additional resuscitation at birth - Need for respiratory support - Type of respiratory support needed - Type of treatment for hypoglycemia - Lowest blood glucose measurement within 48 hours post-birth - Intracranial hemorrhage - Neonatal seizures - Necrotizing enterocolitis | **Primary Maternal**  Our primary outcome will be a composite of severe maternal morbidity determined by an expert panel, comprising:   - Maternal mortality (all cause) - Eclampsia - HELLP syndrome - Stroke - Cortical blindness - Retinal detachment - Pulmonary oedema - Placental abruption - Liver rupture - Need for dialysis - Need for extracorporeal membrane oxygenation (ECMO)   *Note: We do not have reliable ascertainment of ICU/HDU admission data. By instead including only severe morbidities which can reasonably be attributed to hypertensive disorders, we will provide a more accurate picture of the effect of disease-modifying drugs.*  **Primary Perinatal**  Our primary perinatal outcome will be a composite outcome determined by expert consensus. This will comprise.   - Stillbirth (fetal death ≥20 weeks’ gestation) - Neonatal death (death within 28 days of birth) - Severe neonatal morbidity, including:   - Bacterial sepsis   - Birthweight < 3^rd^ centile   - Cardiac arrest   - Hypoxic-ischemic encephalopathy (HIE)   - Intracranial hemorrhage   - Necrotizing enterocolitis   - Neonatal asphyxia   - Neonatal seizures   - Requirement for intubation or mechanical ventilation   - Requirement for resuscitation (mechanical or non-mechanical)   *Note: We do not have reliable ascertainment of NICU admission data. Many infants who are born following hypertensive pregnancies will be admitted to NICU without any other severe morbidities. By instead including only diagnosed severe morbidities, we will provide a more accurate picture of the effect of disease-modifying drugs.*  **Secondary Maternal**  *Note: Variables denoted with a * are reported with treatment effect and 95% CI, all others are exploratory only and described with summary statistics*.   - Pregnancy prolongation (time from first antihypertensive dispensation to birth)* - Need for additional antihypertensive(s)* - Individual components of the primary composite outcome - Disease progression (new diagnosis of preeclampsia after randomization)   **Secondary Perinatal**  *Note: Variables denoted with a * are reported with treatment effect and 95% CI, all others are exploratory only and described with summary statistics*. *** Indicates core secondary outcome.*   - Preterm birth (<37; <34; <32; and <28 weeks’ gestation)** - Major congenital anomaly (as defined by EURO-CAT)* - Neonatal hypoglycemia* - Respiratory distress - Neonatal hypothermia - Individual components of primary composite outcome - Birthweight <10^th^ centile |

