| **(F) Causal contrasts of interest** | **Binary Outcomes**  Relative risk (RR) and risk difference (RD) of each outcome (point estimate RR 95% CI) | **Causal comparison:**  *What is the causal effect of exposure to nifedipine during pregnancy on adverse maternal and perinatal outcomes, compared with exposure to labetalol?*  **Estimand = Average treatment effect (ATE)**  Relative risk (RR) and risk difference (RD) of developing each adverse outcome (ATE RR 95% CI).  ***Estimator model*** *–*Doubly robust inverse probability weighting with regression adjustment. |

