**Developing a causal model using directed acyclic graphs (DAGs) to both identify and summarise causal pathways.**

1. Potential confounders will be determined by the above-named authorship team (a quorum of specialists with expert knowledge). All potential confounders are pre-exposure or at exposure.
   1. Covariates to be included in the selection model:
      1. Type of hypertension (gestational hypertension, chronic hypertension, preeclampsia)*
      2. Maternal diabetes mellitus (yes/no)*
      3. Plurality (1/2+)*
      4. Pre-existing renal disease
      5. Pre-existing autoimmune disease
      6. Maternal smoking during pregnancy
      7. Maternal body mass index
      8. IVF/ART conception
      9. Maternal socioeconomic status (SEIFA quintile)
      10. Maternal age at delivery
      11. Mode of birth (neonatal outcomes only)

*Variables denoted with * are included in the Giant PANDA randomization algorithm.*

**Causal pathway and confounding** (excerpt from Causal Inference, What if. M Hernan & J Robins p85: <https://www.hsph.harvard.edu/miguel-hernan/causal-inference-book/>)

*“...the bias has the same structure: it is due to the presence of a cause (known covariate L or unknown covariate U) that is shared by the treatment A and the outcome Y, which results in an open backdoor path between A and Y. We refer to the bias caused by shared causes of treatment and outcome as confounding…”*

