**Define treatment strategy (exposure), assignment procedures, and follow-up period.**

1. The target trial would randomize at the point of diagnosis of a hypertensive disorder of pregnancy (chronic hypertension, gestational hypertension, or preeclampsia). Women would be randomized in a 1:1 ratio to either labetalol or nifedipine. Follow-up would be until 28 days postpartum, and reasons for drop out would include non-adherence to medication, failure to provide consent, unplanned crossover of participants, and random loss to follow up.
2. In the emulated trial, women will be ‘randomized’ at the point of first dispensation of either labetalol or nifedipine at or beyond 11 weeks’ gestation. We will exclude women who were taking both medications prior to 11 weeks’ gestation (unable to be randomized). We will exclude hypertensive women who received neither labetalol or nifedipine (contraindication or non-indication; this cohort will be described). We will also exclude women without hypertension who received labetalol or nifedipine (this cohort will be described).

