3. Total number of dose(s) of allocated antihypertensive drug (mean, SD)
4. In the target trial, there were several **secondary perinatal outcomes** (see *Target Trial Emulation* Table Sfor full list). In our emulation, we will report the following secondary outcomes with treatment effect and 95% confidence intervals (CI):
   1. Preterm birth <37; <34; <32; and <28 weeks’ gestation (yes/no)
   2. Birthweight ≤3^rd^ centile (yes/no)
   3. Neonatal hypoglycemia (yes/no)
   4. Major congenital anomaly as defined by EURO-CAT (yes/no)

Additionally, the following outcomes will also be reported in an exploratory capacity (i.e., with summary statistics only):

1. Individual components of the primary composite outcome (all yes/no)
2. Birthweight <10^th^ centile (yes/no)
3. Mode of birth (spontaneous vaginal, operative vaginal, elective caesarean section, emergency caesarean section)

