**Causal contrasts of interest**

1. **Estimand**

**Maternal outcomes** – relative risk (RR) and risk difference (RD) of primary composite outcome and pre-specified (*) secondary outcomes (ATE RR, 95% CI).

**Neonatal outcomes** – relative risk (RR) and risk difference (RD) of primary composite outcome and pre-specified (*) secondary outcomes (ATE RR, 95% CI).

In the Giant PANDA RCT, the primary neonatal binary outcome is estimated using a type of logistic regression (log-binomial) model. We will use a logistic regression model with robust standard errors (to adjust for maternal clustering). This model provides predictive probabilities that are then used to calculate both the between exposure difference (RD) and relative risk (RR) for all binary and highlighted (*) secondary outcomes.

In our emulated target trial, the estimand is the average treatment effect (ATE) between exposures, presented using both RD and RR metrics. Within the potential outcomes framework, a causal interpretation can be made under the assumptions of counterfactual consistency, ignorability (conditional exchangeability), and positivity. Counterfactual consistency means that the definition of exposure is consistent for all individuals. Ignorability states that treatment assignment can be considered exchangeable (i.e. as if the assignment was randomized) after controlling for, or conditioning on, a set of covariates. This implies that there are no important unmeasured confounders, an untestable assertion. The positivity assumption means that, for all observations, the conditional probability of being exposed and of not being exposed (receiving treatment or not receiving treatment) are both greater than zero.

1. **Estimators**

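### The planned selection model for neonatal outcomes includes mode of birth, a post-treatment variable; the reported primary propensity model does not, and plan and report must be reconciled

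*SAP*

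**What the plan says.** - **Covariate list** (SAP, Developing a causal model using directed acyclic graphs). Under "Covariates to be included in the selection model" there are eleven items. The last is "Mode of birth (neonatal outcomes only".
- **Rule for that list** (same section, item 1). "All potential confounders are pre-exposure or at exposure".
- **Time zero** (Define treatment strategy). Women enter the emulated trial "at the point of first dispensation of either labetalol or nifedipine". The Target Trial Emulation table places this between 11+0 and 36+6 weeks.
- **Mode of birth as an outcome** (Outcome definitions). The exploratory perinatal outcomes include "Mode of birth (spontaneous vaginal, operative vaginal, elective caesarean section, emergency caesarean section". In the target-trial column of the emulation table it is a starred secondary outcome, reported there with a treatment effect.
- **Mode of birth as baseline** (Part One table). It also appears under the neonatal baseline heading.
- **Estimand and estimator.** "In our emulated target trial, the estimand is the average treatment effect (ATE) between exposures". The estimator is given as "Doubly robust inverse probability weighting with regression adjustment". No direct-effect or mediation estimand is named.
- **Reported model** (Details of primary analysis models). The neonatal balance table has rows for hypertensive subtype, comorbidities, parity, smoking, plurality, ART/IVF, SEIFA, age and body mass index. It has no row for mode of birth.

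**The concern.** How a baby is delivered cannot influence which drug was dispensed earlier in the pregnancy. Mode of birth therefore fails the definition of confounding that the SAP itself quotes, a cause shared by treatment and outcome. It may instead be a consequence of treatment, through blood pressure control, disease progression and the decision to deliver.

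Conditioning on such a variable has two possible effects. It blocks whatever part of the drug effect passes through mode of birth. Because disease severity and fetal compromise plausibly drive both mode of birth and neonatal outcome, it can also create an association between drug and outcome where none exists. The composite adds a difficulty: stillbirth and very low birthweight centile can arise before delivery and influence how delivery happens, so the covariate may partly follow from the outcome.

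Double robustness gives no protection. It covers misspecification of one of the two submodels, not a covariate set that is wrong for the estimand. As worded, the item covers every neonatal outcome. It therefore reaches the primary composite and also the secondary outcomes reported with effects: preterm birth, birthweight at or below the 3rd centile, hypoglycemia and major anomaly.

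**Working it through.** **1. Order in time.** First dispensation falls at 11+0 to 36+6 weeks of a continuing pregnancy, and mode of birth is known only at its end. It is after exposure for every woman. The rule and the listed item cannot both stand.

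**2. Plan against reported model.**

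| | Covariate list | Neonatal balance table |
|---|---|---|
| Mode of birth | listed, neonatal only | absent |
| Parity | not listed | present |

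The neonatal table has the same rows as the maternal one. Only the primary models are shown. Outcome-model covariates are left to the DAG (section B, Outcome model using regression adjustment), whose figure is not available here.

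**3. Size.** The SAP gives no figure on this point. Its detectable difference for the neonatal primary outcome (5.6 points, Anticipated sample size) comes without alpha, power or baseline rate, and the argument does not use it. What follows is an exact population calculation in which **every input is an assumption**, except that the 10% on nifedipine matches the SAP's approximate split.

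- Treatment A: 10% treated, independent of severity U (30% prevalence).
- Mode of birth M (binary): logit P(M=1) = −0.4 + a·A + u₁·U.
- Outcome Y, with no direct effect of A: logit P(Y=1) = −1.6 + m·M + u₂·U.
- True RD = P(Y|A=1) − P(Y|A=0).
- M-adjusted RD = Σ over M of P(M)·[P(Y|A=1,M) − P(Y|A=0,M)].

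Three settings:
- mediation only: m = 0.7, u₁ = u₂ = 0
- collider only: m = 0, u₁ = u₂ = 1.2
- both: m = 0.7, u₁ = u₂ = 1.2

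True RD → M-adjusted RD, in percentage points:

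| a (log-OR, drug on M) | Mediation only | Collider only | Both |
|---|---|---|---|
| −0.8 | −2.06 → 0 | 0 → +1.07 | −2.43 → +1.21 |
| −0.4 | −1.11 → 0 | 0 → +0.54 | −1.25 → +0.61 |
| 0 | 0 → 0 | 0 → 0 | 0 → 0 |
| +0.4 | +1.19 → 0 | 0 → −0.50 | +1.24 → −0.57 |
| +0.8 | +2.39 → 0 | 0 → −0.94 | +2.41 → −1.08 |

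Hand check of the first mediation cell: P(M) is 0.401 untreated and 0.231 treated, a difference of −0.170. P(Y) is expit(−0.9) = 0.289 with M and expit(−1.6) = 0.168 without, a difference of 0.121. The product is −0.170 × 0.121 = −0.0206.

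The largest distortion is 1.21 − (−2.43) = 3.64 points. It is zero throughout the row in which the drug does not change mode of birth. Leaving M out returns the true RD in every cell.

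**The case against.** The strongest reply is that the reported neonatal primary propensity model does not contain mode of birth. A reader of the covariate list might infer that the primary perinatal ATE is already biased. The documents do not support that. The balance table has no such row, and its overidentification test has 10 degrees of freedom against 11 for the maternal model, which gives no hint of an added term. This part of the reply stands. It does not clear the plan: the secondary neonatal models are not shown, the outcome-model covariates cannot be seen, and the departure from the list is unexplained.

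A reader might also infer that adjustment must remove part of any drug effect. Only a part acting through mode of birth could be removed, and the documents do not show that nifedipine and labetalol differ in their effect on it. But the plan cannot presume there is none while studying mode of birth as an outcome.

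A third temptation is to attach a size. For example, an assumed 10-point difference in emergency caesarean times an assumed 25-point risk gap gives 0.10 × 0.25 = 2.5 points, or 0.025/0.056 = 45% of the stated detectable difference. All the rates are invented, and the product treats the whole risk gap as caused by mode of birth although shared severity would account for some of it. That figure should not be used.

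Finally, an elective caesarean may be planned before the first dispensation. That does not rescue the variable as defined, which also includes emergency caesarean and operative vaginal birth.

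**Conclusion.** The plan contains a specification error in the covariate set for a primary outcome. A post-treatment variable is listed for the neonatal selection model, against the plan's own timing rule, its own use of that variable as an outcome, and a total-effect ATE. This follows from the text alone.

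The consequence is conditional. Bias needs a drug effect on mode of birth, together with either an effect of mode of birth on the outcome or unmeasured causes common to both. The documents give no magnitude. The 0 to 3.64 points above show the mechanism under assumed inputs, including a possible reversal of sign, and do not estimate bias in this study.

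The error is shown for the plan and not for the reported primary selection model. Whether mode of birth entered the outcome model or any secondary neonatal model cannot be settled from these documents.

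**What to change.** 1. Delete mode of birth (item 11) from the selection-model list.
2. State that mode of birth, and other variables that treatment can affect, enter neither the selection nor the outcome model for any neonatal ATE. Word the rule by what treatment can affect, not by recording date alone, so that it does not catch maternal age at delivery or smoking during pregnancy. Use as an auxiliary variable for imputation is a separate matter and need not be barred.
3. Keep mode of birth only as the exploratory perinatal outcome, and move it out of the neonatal baseline block of the Part One table.
4. Reconcile the list with the reported model: record that mode of birth was not in the primary propensity model, justify adding parity, and list the outcome-model covariates and those of the secondary neonatal models.

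The cost is a few lines of text and a short covariate table, with no new data. Any outcome or secondary neonatal model that did include mode of birth would have to be rerun without it.

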**Define populations (target, source, and study).**

- 1. The target trial population is all pregnant women, with access to obstetric services, who have diagnosed or suspected hypertensive disorders of pregnancy after 11 weeks’ gestation.
  2. The target trial source population is all women who gave birth in Victoria between 2009 – 2020.
  3. In the emulated target trial, our source population will include all hypertensive women (with gestational hypertension, chronic hypertension, or preeclampsia) who gave birth in Victoria between 2009 – 2020, who received a dispensation of labetalol or nifedipine between 11+0- and 36+6-weeks’ gestation.

**Define treatment strategy (exposure), assignment procedures, and follow-up period.**

1. The target trial would randomize at the point of diagnosis of a hypertensive disorder of pregnancy (chronic hypertension, gestational hypertension, or preeclampsia). Women would be randomized in a 1:1 ratio to either labetalol or nifedipine. Follow-up would be until 28 days postpartum, and reasons for drop out would include non-adherence to medication, failure to provide consent, unplanned crossover of participants, and random loss to follow up.
2. In the emulated trial, women will be ‘randomized’ at the point of first dispensation of either labetalol or nifedipine at or beyond 11 weeks’ gestation. We will exclude women who were taking both medications prior to 11 weeks’ gestation (unable to be randomized). We will exclude hypertensive women who received neither labetalol or nifedipine (contraindication or non-indication; this cohort will be described). We will also exclude women without hypertension who received labetalol or nifedipine (this cohort will be described).

**Outcome definitions – primary and secondary outcomes.**

1. In the target trial, the **primary maternal outcome** is severe hypertension (systolic blood pressure ≥160mmHg). We do not have reliable access to blood pressure measurements; however, our much larger sample size allows us to investigate downstream effects of severe hypertension (severe morbidity). Therefore, the primary maternal outcome will be a composite comprising:
   1. Maternal mortality (all cause) (yes/no)
   2. Eclampsia (yes/no)
   3. HELLP syndrome (yes/no)
   4. Stroke (yes/no)
   5. Cortical blindness (yes/no)
   6. Retinal detachment (yes/no)
   7. Pulmonary oedema (yes/no)
   8. Placental abruption (yes/no)
   9. Liver rupture (yes/no)
   10. Need for dialysis (yes/no)
   11. Need for extracorporeal membrane oxygenation (ECMO) (yes/no)
2. In the target trial, the **primary perinatal outcome** is a composite of stillbirth (≥20 weeks’ gestation), neonatal death (≤28 days post-birth), and neonatal unit admission requiring separation of the infant and mother. We will maintain this outcome by reporting a primary perinatal outcome comprising:
   1. Stillbirth ≥ 20 weeks’ gestation (yes/no)
   2. Neonatal death ≤ 28 days post-birth (yes/no)
   3. Severe neonatal morbidity, comprising:
      1. Neonatal seizures (yes/no)
      2. Necrotizing enterocolitis (yes/no)
      3. Hypoxic-ischemic encephalopathy (yes/no)
      4. Birthweight <3^rd^ centile (yes/no)
      5. Bacterial sepsis (yes/no)
      6. Intracranial hemorrhage (yes/no)
      7. Neonatal asphyxia
      8. Cardiac arrest (yes/no)
      9. Requirement for mechanical or non-mechanical resuscitation (yes/no)
      10. Requirement for intubation or mechanical ventilation (yes/no)
3. In the target trial, there were several **secondary maternal outcomes** (see *Target Trial Emulation* Table Sfor full list). As these secondary outcomes are largely accounted for in our primary composite outcome, we will report the following secondary outcomes with treatment effect and 95% confidence intervals (CI):
   1. Need for additional antihypertensives (yes/no)
   2. Progression from gestational hypertension to preeclampsia (yes/no)

Additionally, the following outcomes will also be reported in an exploratory capacity (i.e., with summary statistics only):

1. Individual components of the primary outcome (all reported as yes/no)
2. Hospital admission prior to 37 weeks’ gestation (yes/no)
3. Total number of dose(s) of allocated antihypertensive drug (mean, SD)
4. In the target trial, there were several **secondary perinatal outcomes** (see *Target Trial Emulation* Table Sfor full list). In our emulation, we will report the following secondary outcomes with treatment effect and 95% confidence intervals (CI):
   1. Preterm birth <37; <34; <32; and <28 weeks’ gestation (yes/no)
   2. Birthweight ≤3^rd^ centile (yes/no)
   3. Neonatal hypoglycemia (yes/no)
   4. Major congenital anomaly as defined by EURO-CAT (yes/no)

Additionally, the following outcomes will also be reported in an exploratory capacity (i.e., with summary statistics only):

1. Individual components of the primary composite outcome (all yes/no)
2. Birthweight <10^th^ centile (yes/no)
3. Mode of birth (spontaneous vaginal, operative vaginal, elective caesarean section, emergency caesarean section)

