**Target Trial Emulation**

| **(A) Research Question** | ***What is the causal effect of exposure to nifedipine on adverse maternal and neonatal outcomes, compared with exposure to labetalol?*** | |
| --- | --- | --- |
|  | **Target Trial (Giant PANDA)** | **Emulation** |
| **(B) Populations** | All women with hypertensive disorders of pregnancy (chronic hypertension, gestational hypertension, or preeclampsia) requiring antihypertensive medication at gestational age 11^+0^-19^+6^; 20^+0^-27^+6^; and 28^+0^-36^+6^.  *Exclusions:* contraindication to labetalol or nifedipine; on both labetalol and nifedipine prior to randomization; unable to provide informed consent; unable to be randomized. | All women with hypertensive disorders of pregnancy (gestational hypertension, chronic hypertension, or preeclampsia) requiring antihypertensive treatment (dispensed labetalol or nifedipine) between 11^+0^ and 36^+6^ weeks’ gestation.  *Exclusions:* Taking both labetalol and nifedipine prior to 11 weeks’ gestation. |
| **(C) Treatment strategies** | Primary  Intention-to-treat (ITT): All women randomized to labetalol or nifedipine, regardless of discontinuation or crossover of treatment groups.    Sensitivity  Per-protocol: All women randomized to labetalol or nifedipine, who continued with assigned treatment until no longer indicated.  On-treatment: All women randomized to labetalol or nifedipine, who continued with assigned treatment until no longer indicated and who self-reported ≥90% adherence across all study contacts. | Primary  Intention-to-treat (ITT): All women who received ≥1 prescription and dispensation of labetalol or nifedipine, including those who received both medications during the study period (crossover will be determined by timing of dispensation) and those who discontinued treatment.  *Crossover defined as receiving both labetalol and nifedipine between 11-36 weeks’ gestation.*  Sensitivity  Per-protocol: All women who received ≥1 prescription and dispensation of labetalol or nifedipine during the study period, but did not receive both medications at any time. |
| **(C) Assignment procedures** | Randomized at diagnosis of hypertension requiring medical intervention (1:1 ratio of nifedipine/labetalol). | “Randomized” (via inverse probability weighting) at point of first dispensation of labetalol or nifedipine during the study period (≥11 weeks’ gestation and ≤36+6 weeks’ gestation). |

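### Use of other antihypertensives before time zero is absent from the listed covariates and fitted propensity models, so first-line and add-on users of the study drugs are treated as exchangeable.

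*SAP*

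**What the plan says.** **Entry.** The assignment row of the Target Trial Emulation table places emulated randomization "at point of first dispensation of labetalol or nifedipine during the study period". The section on treatment strategy, assignment and follow-up says the same: "women will be ‘randomized’ at the point of first dispensation of either labetalol or nifedipine at or beyond 11 weeks’ gestation". The source population is hypertensive women "who received a dispensation of labetalol or nifedipine between 11+0- and 36+6-weeks’ gestation". None of these asks that the drug be the woman's first antihypertensive.

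**Exclusion for earlier drug use.** There is one: "Taking both labetalol and nifedipine prior to 11 weeks’ gestation". It also appears in the flow-chart section and in the section on treatment strategy. Other agents are not mentioned.

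**Adjustment.** The section on DAGs lists eleven selection covariates: hypertension type, diabetes, plurality, renal disease, autoimmune disease, smoking, body mass index, IVF/ART, SEIFA quintile, maternal age and, for neonatal outcomes, mode of birth. It adds that "All potential confounders are pre-exposure or at exposure". The balance tables under Details of primary analysis models show subtype, comorbidities, parity, smoking, plurality, ART/IVF, SEIFA, age and body mass index. Antihypertensive use before time zero is in neither place, nor in the Part One baseline table.

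**Outcome.** Among the secondary maternal outcomes is "Need for additional antihypertensives (yes/no"), under the statement that "we will report the following secondary outcomes with treatment effect and 95% confidence intervals (CI"). No drug list, at-risk set or time window is attached to it.

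**The concern.** A woman given labetalol or nifedipine on top of, or in place of, another agent starts follow-up alongside a woman receiving her first drug. These women may differ in disease severity in ways the measured covariates do not capture. The plan has no reliable blood pressure data (Outcome definitions, item 1), so earlier treatment is one of the few severity markers that dispensing records could supply. The causal reading depends on there being no important unmeasured confounders (Causal contrasts of interest). If one drug is more often the add-on, both primary effects and the secondary effects inherit a severity difference that weighting has not been asked to remove.

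The additional-antihypertensive outcome has a second exposure to the same problem. Unless the agent must be new, continued use of a drug already in hand at time zero can be recorded as an event.

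**Working it through.** The plan gives no figure for this point and no prevalence of earlier antihypertensive use, so there is nothing to reproduce. The check has three parts.

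**1. Can an add-on user enter, and is she identified?** She has a study-drug dispensation in the window, so she is eligible. She has not taken both study drugs before 11 weeks, so she is not excluded. No listed covariate or balance-table row records her other drug. The per-protocol analysis removes only women who received both study drugs. The Part Three subgroups (hypertension type, timing of randomization, timing of birth) do not separate treatment line.

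**2. Confounding of the main effects under no true effect.** Let pN and pL be the shares of nifedipine and labetalol women already on another agent, and k their risk ratio for the outcome. The shares and k are assumptions, to be read as what remains after weighting and adjustment.

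- Apparent RR = [1 + pN(k − 1)] / [1 + pL(k − 1)].
- Standardised difference = (pN − pL) / √{[pN(1 − pN) + pL(1 − pL)] / 2}.

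With k = 1.5:

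| pN v pL | Apparent RR | Standardised difference |
|---|---|---|
| 16% v 10% | 1.08/1.05 = 1.03 | 0.06/√0.1122 = 0.18 |
| 20% v 10% | 1.10/1.05 = 1.05 | 0.10/√0.125 = 0.28 |
| 30% v 10% | 1.15/1.05 = 1.10 | 0.20/√0.15 = 0.52 |

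For comparison, the largest raw standardised differences in the balance tables are 0.1759 (maternal) and 0.1889 (neonatal), both for ART/IVF conception. Chronic hypertension shows 0.0536 and 0.0459. The first row is therefore about as unbalanced as the worst measured covariate; the other two are roughly 1.5 and 3 times that. Reversing the first row gives 1.05/1.08 = 0.97.

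**3. The additional-drug outcome, if existing use were counted.** Let b be the share already on another agent and r the risk of a new one, equal in both arms. Then P(yes) = b + (1 − b)r, and the spurious risk difference is (bN − bL)(1 − r). With assumed b of 10% (nifedipine) v 5% (labetalol) and r = 10%:

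- nifedipine: 0.10 + 0.90 × 0.10 = 19.0%
- labetalol: 0.05 + 0.95 × 0.10 = 14.5%
- risk difference +4.5 points, RR 1.31.

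Reversing the shares gives −4.5 points and RR 0.76. Equal shares give 0 and 1.00. Here 10% v 5% is a standardised difference of 0.05/√0.06875 = 0.19, again near the measured maximum. Counting only new agents removes this artefact; confounding of the kind in part 2 could remain.

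**The case against.** **Eligibility follows the target.** The target trial column lists only use of both study drugs among its prior-drug exclusions, so admitting women on other agents is faithful emulation. This stands: the eligibility rule is not the error. What differs is that randomization would balance baseline agents, whereas weights can be relied on only for what enters them.

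**The measured covariates already carry much of this.** Subtype and comorbidities are in the models and well balanced after weighting, and subgroups by hypertension type are planned. This stands in part. They are proxies, and within chronic hypertension, for example, they do not tell a first-line user from an add-on user.

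**Additional may simply mean new.** A reader might infer that existing users are counted as events and that the result is off by the full gap in prevalence. The SAP does not say so, nor does it say in words that the outcome is analysed in every woman; that is inferred from the absence of a restriction. The fair statement is that the wording permits such counting. On its own this would be little more than a missing detail, and settling it leaves the adjustment gap untouched.

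**The visible record is incomplete.** The outcome model takes its variables from DAGs whose figures are not shown, and balance tables are given only for the two primary models. A term elsewhere cannot be ruled out, but neither the covariate list nor the tables contain one.

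**Conclusion.** The adjustment gap is real and worth closing. Its size and direction cannot be derived from the SAP. At an imbalance like the worst among the measured covariates and an assumed 1.5-fold risk, the distortion of a null relative risk is small, about 1.03. It reaches 1.05 to 1.10 only with imbalance well beyond anything in the balance tables. An unmeasured factor could be that unbalanced, so those values are a range and not a forecast. If baseline use is equal in the two arms, there is no bias from this source.

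A reader might go further and conclude that the primary effects are known to be biased, or that earlier treatment is the best severity marker in these data. The SAP supports neither: it gives no data on earlier treatment and nothing that ranks it against other markers. The additional-drug outcome is the more sensitive result, but only on the reading in which existing use counts.

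**What to change.** - From PBS, derive a flag for any antihypertensive other than labetalol or nifedipine dispensed in a fixed look-back before time zero (for example 90 days). It is a pre-exposure variable, so it meets the plan's own condition for confounders.
- Report the flag by arm in the baseline table.
- Add it to the selection, outcome and imputation models.
- Add a sensitivity analysis restricted to women with no other agent at baseline.
- Define need for additional antihypertensives as an agent first dispensed after time zero and before birth that was not in use at time zero. State also whether crossover to the other study drug counts.

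**Cost.** One derived variable and one more propensity term, with a nifedipine arm of about 750 (10% of about 7,500). The bootstrap-imputation models (B = 1000, M = 2) would have to be rerun. The sponsor must first confirm that the PBS extract covers other antihypertensives, because the Data Sources section describes its use only for the two study drugs. The additional-antihypertensive outcome itself needs data on other agents, so some source must already be intended.
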